### 2.2. Eligibility Criteria

Participants aged 60 or over will be enrolled at elderly social centers of the city of Murcia (Region of Murcia, Spain). Participants self-reporting severe cardiovascular problems such as heart valve disease, uncontrolled heart rhythm problems, automatic defibrillator, and pacemakers will be excluded. Additionally, participants with a Barthel score less than 90, less than 3 points in the Mini-Cog test, or those who are unable to stand up from a chair without assistance will be excluded from this study. All participants will provide written informed consent to participate in this study.

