### 2.4. General Data Collection

All data collection will be performed at the same day. Data relative to age and sex of the subjects will be collected in form of self-reported questionnaire. Moreover, the following information will be collected through a list of observations: presence of depressive symptoms, socioeconomic status, education level, presence of comorbidity, polypharmacy, number of falls in the last year, number of hospitalizations in the last year and smoking habits. All data will be registered by a single researcher in a spreadsheet and then cross-checked point by point from the original data register by another researcher. Detailed information about general data collection can be found in Table A1.

The procedure for data collection will be performed in the following order: (i) clinical interview; (ii) index test; (iii) frailty assessment; (iv) sarcopenia assessment.

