### 2.9. Statistical Analysis

The database will be created in Microsoft Excel©, Microsoft Corp., Redmond, WA, USA and the software IBM SPSS Statistics 26.0, SPSS Inc., Chicago, Ill, USA will be used for further analysis. A descriptive analysis of data will be carried out to report the participants’ characteristics. We will provide values represented as mean, standard deviation, and 95% confidence interval (CI) for continuous variables and frequencies and percentages for categorical variables. Kolmogorov–Smirnov’s test will be used to assess the normal data distribution. A data scrub will be performed with range and logic tests and we will search for unknown or unlikely values.

A complete case analysis will be performed. The AUC of the receiver operating characteristic (ROC) will be calculated to identify the best cut-off point of muscle power to discriminate subjects with both syndromes separately and in combination. Then, a multiple logistic regression equation with muscle power and calf circumference or mid upper-limb circumference will be generated and an additional ROC analysis will be performed using predictive probability from the results of the multiple logistic regression analysis to identify the best cut-off point for detecting both syndromes for each sex. Cross-tabulations of the index test with the reference standards (prefrailty and sarcopenia syndromes) will be performed and sensibility, specificity, positive and negative predictive values, and positive and negative likelihood ratios will be calculated. Finally, after classifying the status of the subjects into robust, prefrail, sarcopenia or the combination of both syndromes, the chi-square tests will be used to assess differences in proportion regarding their clinical profile (Table A1) and the Odds Ratio with 95% CI will be calculated.

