## Appendix A

**Table A1 sensors-22-06010-t0A1:** General data collection.

Domain	Question	List of Possible Answers
Health Status	Do you smoke?	Yes/No
	Have you been diagnosed with one or more of these diseases?	Hypertension
		Diabetes Type I or II
		Cardiovascular Disease
		Chronic Obstructive Pulmonary Disease
		Acute Myocardial Infarction
		Cancer
		Asthma
		Bronchitis
		Urinary Incontinence
		Anemia
		Thyroid Disease
		Others
	Do you take five or more pills a day?	Yes/No
	How is your health in general?	Very good
		Good
		Fair
		Bad
		Very bad
Socioeconomic Status	Please, choose the option relative to your study level	None
		Primary
		Lower Secondary
		Upper Secondary
		Bachelor’s or equivalent
		Master’s or equivalent
		Doctorate’s or equivalent
	Please, choose the option that better fits with your annual salary	0–10,000 €
		10,000–20,000 €
		20,000–30,000 €
		30,000–40,000 €
		>40,000 €
Depression	Are you basically satisfied with your life?	Yes/No
	Do you often get bored?	Yes/No
	Do you often feel helpless?	Yes/No
	Do you prefer staying at home instead of going out and doing new things?	Yes/No
	Is it hard for you to get started on new projects?	Yes/No
Adverse Events	Have you experienced two or more falls during the last year?	Yes/No
	Have you been hospitalized during the last year?	Yes/No

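### The clinical-profile odds ratios in 2.9 are crude and may partly reflect age, and Table A1 does not capture the fall and hospitalization counts that 2.4 promises

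*Protocol article*

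**What the plan says.** The comparison comes at the end of section 2.9, "after classifying the status of the subjects into robust, prefrail, sarcopenia or the combination of both syndromes". For these four groups, the plan is: "the chi-square tests will be used to assess differences in proportion regarding their clinical profile (Table A1) and the Odds Ratio with 95% CI". No covariate, stratification or reference group is named, and the step is not labelled exploratory. Elsewhere in 2.9 a logistic regression is specified for the diagnostic index (muscle power with a circumference measure), and its ROC analysis serves "to identify the best cut-off point for detecting both syndromes for each sex". Neither the regression nor the split by sex is carried over to the profile comparison.

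On the data, section 2.2 says "Participants aged 60 or over will be enrolled" and sets no upper limit. Section 2.4 says "Data relative to age and sex of the subjects will be collected in form of self-reported questionnaire". It also lists "number of falls in the last year, number of hospitalizations in the last year" among the variables and points to Table A1 for the detail. Table A1 in Appendix A asks "Have you experienced two or more falls during the last year" with the answers yes and no, and asks about hospitalization in the last year in the same yes/no form.

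**The concern.** The Introduction describes frailty and sarcopenia as bound up with biological ageing, and the sample is open-ended above 60. The robust and combined groups can therefore be expected to differ in age. Falls, hospital stays, chronic disease and polypharmacy may also depend on age. If both links are present, a crude odds ratio mixes what goes with the syndrome and what goes with being older. The Introduction and Discussion discuss added harm when the two syndromes coexist, recurrent falls included, so a reader could take these odds ratios as further evidence of that. Age and sex are already in the dataset, so separating the two needs no new data.

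The falls and hospitalization fields raise a different problem. The text promises counts and the form collects categories. Once the data are collected this way, no analysis can recover a count, and a person with one fall cannot be told from a person with none.

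**Working it through.** **1. Is the step unadjusted as written?** Yes. It consists of chi-square tests and odds ratios, and the only regression in 2.9 belongs to the diagnostic index.

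**2. Can the size of the age effect be taken from the article?** No. It gives no age distribution, no age difference between groups and no age association for any Table A1 item. Everything in steps 3 and 4 rests on assumed inputs.

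**3. Rough calculation.** If the combined group is *g* years older than the robust group, and the log-odds of an item rise by *b* per year with no syndrome effect, the crude odds ratio is about exp(*g* × *b*).
- *g* = 5, *b* = 0.03: exp(0.15) = 1.16
- *g* = 10, *b* = 0.05: exp(0.50) = 1.65

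**4. Simulation.** The total of 400 participants and the 13% for the combined group come from section 2.8. The other inputs are assumptions:
- ages from 60 to 95, centred near 73;
- group shares at age 73 of 40% robust, 37% prefrail, 10% sarcopenic and 13% combined;
- a yes/no item with 25% prevalence at age 73;
- item and group independent given age;
- 400 runs per setting.

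The table gives the median crude odds ratio, combined versus robust, with the rejection rate of the four-group chi-square test at 0.05 in brackets. The article states no test level for this step, so 0.05 is also assumed.

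| Age OR per 10 years for combined vs robust | Item age OR 1.0 | 1.3 | 1.6 | 2.0 |
|---|---|---|---|---|
| 1.0 | 1.00 (6.2%) | 1.05 (5.0%) | 1.02 (3.0%) | 0.97 (2.8%) |
| 1.5 | 1.02 (7.2%) | 1.07 (7.0%) | 1.11 (7.2%) | 1.15 (5.2%) |
| 2.0 | 1.04 (4.2%) | 1.11 (5.8%) | 1.21 (4.8%) | 1.28 (7.5%) |
| 3.0 | 1.03 (4.8%) | 1.12 (6.2%) | 1.35 (9.8%) | 1.50 (14.2%) |
| 4.0 | 0.97 (4.8%) | 1.22 (7.0%) | 1.39 (11.0%) | 1.61 (18.5%) |

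With 400 runs, the Monte Carlo standard error of a true 5% rate is √(0.05 × 0.95 / 400) = 1.1 percentage points, so small departures from 5% are noise. With age in a logistic model, the odds ratio lies between 0.94 and 1.03 and the rejection rate between 3.5% and 7.5% in all 20 settings. The simulation did not model sex.

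If either age link is absent, there is no bias. With moderate links (1.5 to 2.0 for group, 1.3 to 2.0 for item), the crude odds ratio is 1.07 to 1.28 and rejection stays at about 5% to 8%. Only with strong links (3 to 4 for group, 1.6 to 2.0 for item) does it reach 1.35 to 1.61, with rejection of about 10% to 19%.

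**5. Number of comparisons.** Table A1 has 13 questions, one of which, "Have you been diagnosed with one or more of these diseases", offers 12 disease answers. Counting these one by one gives 1 smoking + 12 diseases + 1 pills + 1 general health + 1 education + 1 income + 5 depression + 2 adverse events = 24 items. If no item differs and the tests are independent at 0.05:
- 24 items: 24 × 0.05 = 1.2 chance findings expected; at least one with probability 1 − 0.95^24 = 0.71
- 13 questions: 13 × 0.05 = 0.65 expected; 1 − 0.95^13 = 0.49

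For 24 items, a common correlation between test statistics of 0.2 or 0.4 lowers 0.71 to about 0.65 or 0.53.

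**6. Section 2.4 against Table A1.**

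| Variable | Section 2.4 | Table A1 | Lost |
|---|---|---|---|
| Falls, last year | number | two or more: yes/no | 0 and 1 merged; 2, 3 and more merged |
| Hospitalizations, last year | number | any: yes/no | 1, 2 and more merged |

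This disagreement depends on no assumption.

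**The case against.** The strongest reply is that the step only describes how the groups differ, and crude proportions do that correctly. If the combined group is older and takes more pills, the difference in proportion is real and not a false positive. Nothing in the article calls these odds ratios causal or independent of age, and its statements on added risk cite other studies. This stands, and is why the crude proportions should stay.

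A reader might infer that the differences will largely reflect age. The documents do not support that: they give no age figures, and the range in the working runs from no bias to about 1.6.

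A reader might also infer from the 71% that some findings are bound to be false. That figure needs 24 independent items, none of which differs. Section 2.4 lists comorbidity and depressive symptoms as single variables, eight in all, which gives 1 − 0.95^8 = 0.34. The figure also sits badly with an argument that many items differ through age. It supports an exploratory label and no more.

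Ordinal models, methods for sparse cells and a formal error-rate rule are commonly left to an analysis plan that is not shown, so their absence from an article is not a fault.

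On falls, the Introduction names recurrent falls as the outcome of interest, which a threshold of two or more captures. Rewording 2.4 would therefore also remove the contradiction. It would leave the loss of information in place.

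**Conclusion.** Two minor points hold. First, the odds ratios specified in 2.9 are crude, for syndromes the article itself links to ageing, with age and sex available. They may partly reflect age by an amount that cannot be known from the article. The range of about 1.0 to 1.6 for a null item is conditional on the assumed age effects, and its upper end needs strong links of age to both group and item. Second, section 2.4 and Table A1 contradict each other on falls and hospitalizations, and the form as drafted loses the counts.

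Both concern a secondary analysis. AUC, cut-offs, sensitivity, specificity, predictive values and likelihood ratios do not depend on it.

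**What to change.** In 2.9, keep the crude proportions by group as description. Add odds ratios from logistic regression with syndrome group as a factor, the robust group as reference, and age and sex as covariates. State that the comparison across Table A1 items is exploratory.

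In Table A1, replace the two yes/no fields with the number of falls and the number of hospitalizations in the last year, as 2.4 says. The two-or-more-falls and any-hospitalization categories can still be derived from the counts.

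The cost is a few lines of analysis text and two answer fields. The downside is slightly wider intervals for adjusted odds ratios in small groups; at 13% of 400 the combined group would hold about 0.13 × 400 = 52 people.

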## 3. Discussion

For years, in order to prevent adverse health-related consequences in older adults, several studies have paid special attention to sarcopenia and frailty syndrome separately. Both syndromes have been used to categorize people according to their risk for developing disability, falls, hospitalizations, and mortality as well as to individualize appropriate interventions in order to revert these pathological conditions. Moreover, the phenotypic and criteria–diagnosis similarities between both syndromes have led to an undistinguished use of both concepts as if they were connected to one another. However, despite of the correlation between frailty and sarcopenia syndromes, recent studies have evidenced that they are distinct disorders [7,8,9,10]. In fact, whereas frailty individuals have shown two-fold increased mortality risk, frailty-sarcopenic individuals have shown more than three-fold mortality risk compared to neither frail nor sarcopenic individuals, highlighting that both syndromes act independently having an additive effect on mortality [7]. Furthermore, mortality risk has been recently reported to be superior in prefrail sarcopenic than prefrail non-sarcopenic individuals and prefrail individuals only experienced disability more frequently than robust one when they were also sarcopenic [10].

Given the growing interest for analyzing both syndromes in combination and the importance of the early identification of frailty (prefrailty status) and sarcopenia to prevent subsequent functional decline, disability, and the increased mortality risk, a clinical affordable easy-to-use diagnostic tool for detecting both syndromes in combination might have implications for prognosis, optimizing care, and planning interventions for community-dwelling older adults. Thus, the aim of this study is to develop and validate an update of the *Sit-to-Stand* App for detecting prefrailty and sarcopenia syndromes in combination in community-dwelling older adults.

Previous studies have analyzed the role of kinematic parameters during sit-to-stand test derived from sophisticated assessment tools such as force plates or inertial measurement units for detecting frailty and sarcopenia syndrome separately [12,13]. These studies have shown high specificity and sensitivity for detecting frailty or sarcopenia [12,13]; however, this technology, although sensitive to these syndromes, is not readily available or affordable for clinical or field-based testing environments and some current methods remain complex, difficult and time consuming to analyze. These characteristics represent barriers for clinicians that requires valid easy-to-use tools with automatic data processing and real-time results without complicated interpretation or instrumentation.

Recent advances in hand-held technology offer an opportunity to assess muscle power during sit-to-stand test through a smartphone mobile application (*Sit-to-Stand* App) based on high-speed video recording at 240 frames per second which can accurately detect the subject’s sit-to-stand motion [14,15]. This affordable technology only requires the use of a smartphone and an adjustable height chair to set starting knee joint position at 90 degrees for standardization purposes, since it is well known that chair height influences test performance [25,26,27]. This application has the potential to identify the rising phase of the sit-to-stand test, i.e., when the body loses contact with the seat and the center of mass is lifted until knee and hip extension is reached which is critical for muscle power calculation [28,29,30], otherwise muscle power could be underestimated. The application converts the time of this phase into muscle power relative to body weight through a regression equation which has been twice prospectively validated against 3D motion capture camera and force plates in community-dwelling older adults [14,15].

Since muscle mass has been related to frailty and sarcopenia syndrome and can be easily measured through calf circumference or upper mid-arm circumference [16,17], the integration of both outcomes (muscle mass and muscle power) into the mobile application will have the potential for detecting prefrailty and sarcopenia with enough accuracy. Thus, the update of this application will provide to the clinicians the ability to determine both syndromes either in combination or separately in a short time period with an easy-to-use interface and automatic data processing overcoming the aforementioned barriers.

Despite a rigorous approach towards data collection and synthesis, this research is not without limitations. First, the retrospective validation design of this study will limit the external validity of the mobile application for diagnosing purposes. However, prior to performing a prospective validation, a retrospective design is necessary. Second, since this study will be focused on people attending elderly social centers, these people are likely to be fitter or healthier than community-dwelling older adults who do not attend these centers. Therefore, the cut-off points estimated for diagnosing these syndromes in this research could be superior than those established in less fit people, so sensitivity and specificity might be influenced.

## 4. Conclusions

Considering the high socioeconomical impact of these syndromes, the creation of a highly reliable tool for detecting sarcopenia and prefrailty status will provide to the scientific community and clinical personnel the possibility to diagnose both syndromes with an easy-to-use interface and automatic data processing in short time periods within the environmental context of daily living. This innovative portable tool will have potential implications for prognosis, optimizing care, and planning interventions. In fact, it is well known that early detection of these syndromes might potentially increase the chances of reversibility.

## Figures and Tables

**Figure 1 sensors-22-06010-f001:**
[figure not shown]
User interface of the App. White dot represents the reflective marker placed on the greater trochanter while the subject is in a sitting position (**top panel**), at the beginning of the vertical movement when the reflective marker crosses the first horizontal grip line on the screen (**middle panel**), and at the end of the vertical movement, when the reflective marker achieves the highest point (**lower panel**).

## Data Availability

Data will be made available upon request from the authors.

## Appendix A

**Table A1 sensors-22-06010-t0A1:** General data collection.

Domain	Question	List of Possible Answers
Health Status	Do you smoke?	Yes/No
	Have you been diagnosed with one or more of these diseases?	Hypertension
		Diabetes Type I or II
		Cardiovascular Disease
		Chronic Obstructive Pulmonary Disease
		Acute Myocardial Infarction
		Cancer
		Asthma
		Bronchitis
		Urinary Incontinence
		Anemia
		Thyroid Disease
		Others
	Do you take five or more pills a day?	Yes/No
	How is your health in general?	Very good
		Good
		Fair
		Bad
		Very bad
Socioeconomic Status	Please, choose the option relative to your study level	None
		Primary
		Lower Secondary
		Upper Secondary
		Bachelor’s or equivalent
		Master’s or equivalent
		Doctorate’s or equivalent
	Please, choose the option that better fits with your annual salary	0–10,000 €
		10,000–20,000 €
		20,000–30,000 €
		30,000–40,000 €
		>40,000 €
Depression	Are you basically satisfied with your life?	Yes/No
	Do you often get bored?	Yes/No
	Do you often feel helpless?	Yes/No
	Do you prefer staying at home instead of going out and doing new things?	Yes/No
	Is it hard for you to get started on new projects?	Yes/No
Adverse Events	Have you experienced two or more falls during the last year?	Yes/No
	Have you been hospitalized during the last year?	Yes/No
